| STATISTICAL ANALYSIS | 
The main statistical technique will be “repeated measurement” mixed models with randomised group as fixed factor. Sex and country are stratification factors used in the randomisation and therefore will be included in the models. Birth weight will be included as covariate in the primary model (i.e., the model on weight gain per day). The impact of factors that may influence the intervention effect may be evaluated by adding them as (time varying) covariates.
 
For concluding equivalence on the primary outcome parameter, the two-sided 90% confidence intervals for the differences in mean weight gain per day from baseline to 17 weeks of age will be calculated. Equivalence between the arms will be demonstrated at the 5% significance level, if the two-sided 90% confidence intervals for the differences in mean weight gain per day between the arms lies entirely between -3 g/day and +3 g/day. The margin of <math>\pm 3</math> g/day will be used if the pooled standard deviation (SD) of test and control group is equal or smaller than 6. If the pooled standard deviation is bigger than 6, an equivalence margin of <math>0.5 \times \text{SD}</math> will be used.
 
Equivalence in a secondary growth parameter is demonstrated at the 5% significance level if a two-sided 90% confidence interval for the difference in mean gain per day from baseline to 17 weeks of age between test and control lies entirely between <math>-0.5 \times \text{SD}</math> and <math>+0.5 \times \text{SD}</math>. SD is the pooled standard deviation of the gain per day (in growth parameter) from baseline anthropometric visit to 17 weeks of age computed from infants receiving test and control product.
 
Equivalence (at week 17) in a secondary z-score growth parameter is demonstrated at the 5% significance level if a two-sided 90% confidence interval for the difference in mean z-score between test and control lies entirely between -0.5 and +0.5.
 
The statistical analyses for the assessment of tolerance, safety parameters, blood parameters will be descriptive.
 |

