| INTERIM ANALYSIS     | 
In order to verify whether the assumptions for the sample size calculations are correct an interim analysis will be performed when it is estimated that approximately 30 evaluable infants per infant formula arm completed the study (until Visit 5). The interim analysis will be performed on the PP data for the primary outcome parameter. In particular, the assumptions on the difference between test and control in weight gain per day from baseline to 4 months and the drop-out/major protocol violators rate will be checked. Since both study products are safe and commercially available there will be no safety interim analysis. Therefore, an independent Data Monitoring Committee will not be installed.
 
In order to maintain the double-blind design of the study, a study independent statistician will perform this interim analysis for checking the sample size assumptions. Based on the results of the interim analysis, an Independent Interim Committee will advise about the number of infants to be recruited. Adaptation of the number of infants to be recruited may occur accordingly. Only upward adaptation of sample size is allowed. The final sample size will be notified via an administrative amendment to the ethical committees. No further protocol changes can be based on this interim analysis.
                                                                                                                                                                                                                                                                                                                                                                                                                                                                                                                                                                                                                                                                                                                                                                                          |

---

|         |                                                                                                                                                                                                                                                               |

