|---------|---------------------------------------------------------------------------------------------------------------------------------------------------------------------------------------------------------------------------------------------------------------|
|         | If the adjusted sample size becomes impractically large, the trial can be stopped for futility. Details of the interim analysis will be described in the Interim Statistical Analysis Plan, which will be finalised before the start of the interim analysis. |
| SPONSOR | Nutricia Research B.V., Utrecht, The Netherlands                                                                                                                                                                                                              |

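### The test-control difference in about 30 infants per arm drives upward re-sizing and a possible futility stop, while the final test stays an ordinary 90% CI at a stated 5% level

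*Protocol*

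**What the plan says.** The Interim analysis row of the protocol synopsis schedules a look at the per-protocol data on the primary outcome once about 30 evaluable infants per formula arm have completed Visit 5. Its purpose is to verify the sample size assumptions. Two items are singled out. One is the treatment effect: "In particular, the assumptions on the difference between test and control in weight gain per day from baseline to 4 months". The other is the proportion of infants lost to drop-out or major violations. The pooled SD is not named.

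The work is given to independent parties: "a study independent statistician will perform this interim analysis for checking the sample size assumptions", and an Independent Interim Committee advises on recruitment. Two consequences follow. "Only upward adaptation of sample size is allowed", and "If the adjusted sample size becomes impractically large, the trial can be stopped for futility". No threshold is given for the second. The row ends: "Details of the interim analysis will be described in the Interim Statistical Analysis Plan, which will be finalised before the start of the interim analysis".

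The Statistical analysis row keeps the usual final rule: "Equivalence between the arms will be demonstrated at the 5% significance level" if the two-sided 90% CI lies within ±3 g/day, or within ±0.5×SD when the pooled SD exceeds 6.

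**The concern.** In an equivalence trial the required size grows roughly as 1/(3 − |d|)², where d is the difference assumed. If the observed d replaces the planned one, chance error in d is magnified. A product with no effect on growth can then appear to need a very large trial, and the synopsis allows the trial to be abandoned for that reason.

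If the trial is enlarged instead, the final size depends on the interim difference. The ordinary CI on the pooled data then no longer has a guaranteed 5% error rate. The choice of d as a driver is made in the protocol. An Interim SAP can add a rule or an adjusted test, but it cannot make a difference from 30 infants per arm precise.

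**Working it through.** **Inputs from the synopsis:** 78 evaluable per arm, 30% drop-out, interim at 30 per arm, margin ±3 g/day, two one-sided tests at 5%, upward-only change.

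**Assumptions, because the synopsis does not give them:** SD 5 or 6 g/day (6 appears only as the margin switch point), re-sizing target 80% power, practical limit 2, 3 or 5 times 78 per arm, size recomputed at the observed d and SD. The margin is held at ±3 in the simulation so that the margin switch does not blur the result.

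**The plan's own figure.** 78/0.70 = 111.4, so 112 per arm and 224 in total, as stated. The 78 is plausible: SD 6, true difference 0.5 and 80% power need 77 per arm. At 78 per arm and zero difference, power is 86% (SD 6) or 96% (SD 5).

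**Precision at the interim.** SE = SD×√(2/30), which is 6×0.258 = 1.55 or 5×0.258 = 1.29 g/day.

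**Required size at SD 6, 80% power.** It is 69, 77, 112, 198 and 446 per arm at d = 0, 0.5, 1.0, 1.5 and 2.0. With a true difference of 0, |d| exceeds 1.0, 1.5 and 2.0 in 52%, 33% and 20% of trials, from 2×[1 − Φ(x/1.55)].

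**Chance of passing the limit.** The limit L is passed when |d| exceeds 3 − (1.645 + 0.842)×SD×√(2/L). For SD 6 and L = 156 this is 3 − 2.487×0.679 = 1.31, and 2×[1 − Φ(1.31/1.55)] = 40%. The other rows follow in the same way. Power and type I error come from simulation (400,000 trials per case). Type I error is taken at a true difference of 3 g/day with the ordinary 90% CI.

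| SD | Limit per arm | Trigger (g/day) | Limit passed, true difference 0 | Power at 0, always stop | Power at 0, extend to limit | Type I error, always stop | Type I error, extend |
|---|---|---|---|---|---|---|---|
| 6 | 156 | 1.31 | 40% | 58% | 97% | 2.6% | 5.7% |
| 6 | 234 | 1.62 | 30% | 68% | 97% | 3.1% | 5.9% |
| 6 | 390 | 1.93 | 21% | 76% | 97% | 3.5% | 6.3% |
| 5 | 156 | 1.59 | 22% | 77% | 99% | 2.9% | 5.8% |
| 5 | 234 | 1.85 | 15% | 84% | 99% | 3.3% | 6.1% |
| 5 | 390 | 2.11 | 10% | 89% | 99% | 3.7% | 6.4% |

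Repeat runs at the smallest limit (SD 6) gave 5.6 to 5.7% for type I error on extension.

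**Combination test.** The two stages are combined with fixed inverse-normal weights √(30/78) = 0.62 and √(48/78) = 0.78. Type I error is then 5.0% in all six cases, and power at zero difference is within 0.2 percentage points of the extend column.

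**Re-sizing on SD only.** With the planned difference fixed at 0 or 0.5, type I error is 5.0 to 5.1% and the chance of passing even twice the planned size is 0.0%. Now apply the synopsis's margin rule. Above SD 6 the margin is 0.5×SD, so margin/SD never falls below 0.5. At difference 0 and 80% power the size is 2×(1.645 + 1.282)²×2² = 68.5, so 69 per arm for every SD of 6 or more. At difference 0.5 it peaks at 77, at SD 6. Both are below 78.

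**The case against.** The strongest reply is that the decision rule is not shown. The synopsis says that assumptions will be checked and that a committee will advise. It does not say that the size is recomputed at the observed d, and it leaves details to an Interim SAP that must be final before the interim. That stands. The percentages above describe one natural rule, and the absence of an error adjustment cannot be claimed.

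A reader might infer that the interim both discards equivalent products and inflates the error rate. The documents do not support that. The two effects belong to opposite branches: always stopping makes the test conservative, and extending raises power to 97 to 99%. The synopsis says only that the trial can be stopped, so it is also not shown that the interim does more harm than good.

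A reader might also quote 20 to 40% as the rate of wrongful stopping. That is the SD 6 result; at SD 5 it is 10 to 22%. An SD of 4 would give 3 to 7% over the same limits, and a 90% power target would raise the SD 6 figures to 26 to 51%. Applying the margin switch at SD 6 moves the stop rates to 36, 27 and 19%.

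Nor is access to unblinded data itself a defect, since it is confined to an independent statistician and committee. Inferring the interim difference from the announced size is speculative, because the drop-out/violator rate also moves that number.

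Finally, an SD-based review seldom changes the size under this margin rule, which may be why SD is not named. That is correct, and the fix must say so. It does not make the interim difference a sound driver.

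**Conclusion.** The concern holds in limited form. The protocol names an estimate with a standard error of about half the margin as a driver of re-sizing and possible stopping. Under the stated assumptions (SD 5 to 6, 80% target, limits of 2 to 5 times 78), the size of the problem depends on what is done when the limit is passed:

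- **Always stop:** about 10 to 40% of trials of a truly identical product end early, and type I error is about 2.6 to 3.7%.
- **Extend to the limit:** power rises, and type I error under the ordinary CI is about 5.6 to 6.4%.

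The stated 5% level is therefore not assured by the protocol text, although the excess is modest and the Interim SAP may deal with it. Calling the error rate uncontrolled would go beyond what the document shows.

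**What to change.** Preferred: base re-sizing on the evaluable (drop-out/violator) rate and the blinded pooled SD. Hold the planned difference fixed and apply the margin rule of the Statistical analysis row as written. Delete the check of the observed difference and the futility stop based on it. State openly that, at an 80% target, the SD review will rarely raise the size above 78 evaluable per arm, so the evaluable rate will mainly govern recruitment.

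Alternative, if difference-based re-sizing is kept: state in the protocol that the final two one-sided tests use an inverse-normal combination with weights set in advance, and give a numeric cap on the sample size. This restores 5.0% type I error with negligible loss of power.

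Either change is a wording change to the protocol and Interim SAP and must be made before the interim. The cost of the preferred option is that there is no early stop on the interim difference and no power gain from extending the trial. The alternative keeps that gain but makes the final analysis more complex.
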